### Sample Size Calculation

The sample size calculation for the multicentre clinical trial will be performed in order to allow for a statistically significant comparison between control and intervention groups at each center with a 95% confidence level, two-tailed analysis and aiming at a reduction in the effect variable, i.e., recurrent cardiovascular events, which is a clinically relevant composite of (i) cardiovascular rehospitalization or urgent visit; or (ii) unplanned revascularization; (iii) cardiovascular mortality; or (iv) worsening heart failure (29, 30). The G Power software was used to determine *a priori* sample size according to the evidence reported in a previous systematic review (5), which showed that eHealth CR was effective reducing rehospitalization [RR = 0.49, 95% CI (0.27, 0.89), *p* = 0.02]. Accordingly, a proportion of 6% in the intervention group was rehospitalized compared with 13% in the control group 1 year after the intervention terminus, resulting in an effect size of 7% (5). Departing from this evidence-based measure of effect size, power (1 -β) of 80%, a significance of 0.05 and accounting for 20% loss to follow-up, a sample of 330 patients per arm will be included.

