## Methods and Analysis

The mHeart.4U trial is designed in accordance with the methodology adopted for mHealth-based interventions for remote monitoring and rehabilitation trials involving CVD patients (5). Accordingly, the study will follow a pragmatic, multicenter, two parallel arms (1:1), prospective, randomized controlled design with blinded endpoint assessment, involving two cardiology units in the Center Region of Portugal. This study is a pragmatic trial because it examines the outcomes of the experimental intervention compared with a standard intervention under circumstances which closely approximate the real world (25). Additionally, personnel undertaking outcome assessment will be blinded to group allocation. The Standard Protocol Items: Recommendations for Interventional Trials reporting guidelines were used to write this protocol (26).

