### Statistical Analysis

The patient characteristics in the two arms at baseline will be compared descriptively using chi-squared tests for the binary and categorical variables and an unpaired Student's *t*-test for the continuous variables. One-sample *t*-test will be performed to measure the differences within the same group.

The primary outcome will be analyzed using a generalized linear mixed model, adjusting for the stratification variables (i.e., gender, hospital unit). Logistic regression will be conducted in order to explore predictive relationships of the baseline categorical variables (e.g., age, clinical variables) on the primary outcomes in both groups.

Analyses to determine the study primary outcome will be performed on the principle of intention-to-treat. Accordingly, assuming there will be a reasonable amount (>5%) of missing data, analyses to determine the primary outcome will be conducted using a multiple imputation model. A per-protocol analysis will be conducted with complete cases to test the robustness of intervention effects under different assumptions. Subgroup analyses will be conducted to determine intervention effects by gender and trial center. All statistical tests will be 2-sided at α = 0.05. The biostatistician will remain blinded throughout the analysis of treatment effects.

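### The sample size is said to support an arm comparison at each center, but 330 per arm is sized for one trial-wide comparison

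*Protocol article*

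**What the plan says.** The protocol article describes one randomized trial with "two parallel arms (1:1") allocation, "involving two cardiology units in the Center Region of Portugal" (Methods and Analysis).

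The Sample Size Calculation section gives the purpose of the calculation as being to "allow for a statistically significant comparison between control and intervention groups at each center", "with a 95% confidence level, two-tailed analysis". Its inputs come from a cited systematic review, in which "a proportion of 6% in the intervention group was rehospitalized compared with 13% in the control group". It adds 80% power, "a significance of 0.05 and accounting for 20% loss to follow-up", and arrives at 330 patients per arm. No total for the trial and no expected number per center is given.

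The Statistical Analysis section analyzes the primary outcome in one generalized linear mixed model for the whole trial, adjusted for gender and hospital unit. Center-specific effects appear only in a later sentence: "Subgroup analyses will be conducted to determine intervention effects by gender and trial center".

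**The concern.** The stated aim is a comparison that can reach significance in each of two centers, yet only one per-arm number is derived and the number of centers does not enter it. If 330 per arm covers the whole trial, each center contributes only part of it and cannot have the power quoted for the whole.

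What is at stake is how center results will be read. A reader told that each center is adequately sized could take significance in one center and not in the other as a real difference between centers. With power near one half in each, that pattern would be common even if the effect were identical in both.

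**Working it through.** **Inputs, all from the protocol article.** Control 13%, intervention 6%, two-sided alpha 0.05, power 80%, loss 20%, 330 per arm (Sample Size Calculation); two arms 1:1 and two centers (Methods and Analysis). The event proportions are taken as the plan states them.

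**Step 1. Reproduce the plan's figure.** Two-proportion formula with pooled variance under the null hypothesis, where p̄ = (0.13 + 0.06)/2 = 0.095:

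n = [1.960·√(2·0.095·0.905) + 0.842·√(0.13·0.87 + 0.06·0.94)]² / 0.07²

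= [1.960·√0.17195 + 0.842·√0.1695]² / 0.0049 = 274.2, rounded up to 275 per arm.

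275 × 1.20 = 330, exactly the stated figure. It is therefore the size of one two-arm comparison, with no factor for two centers. Other formulas give a similar number per comparison before allowance for loss (unpooled variance 272, arcsine 267), so the choice of formula does not hide such a factor.

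**Step 2. Power of the pooled comparison.** With n evaluable per arm,

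power = Φ[(0.07 − 1.960·√(0.17195/n)) / √(0.1695/n)].

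- n = 275: 80.1%.
- n = 330 × 0.80 = 264: 78.5%.

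The small shortfall at 264 arises because the plan multiplied by 1.2; dividing 275 by 0.8 would give 344. That is a separate matter from this point.

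**Step 3. Power per center.** The documents do not state the split, so it is an assumption here.

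| Assumed split | Evaluable per arm | Power |
|---|---|---|
| 50/50, no loss | 165 and 165 | 58.3% in each |
| 50/50, 20% loss | 132 and 132 | 49.2% in each |
| 60/40, 20% loss | 158 and 106 | 56% and 41% |
| 70/30, 20% loss | 185 and 79 | 63% and 32% |

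For n = 132: (0.07 − 1.960·√(0.17195/132)) / √(0.1695/132) = (0.07 − 0.0707)/0.0358 = −0.02, and Φ(−0.02) = 0.49. By Fisher's exact test or with a continuity correction, power at 132 per arm is about 41%.

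The smaller center can hold at most half of each arm. Its power therefore cannot exceed 49% with 20% loss or 58% with none, and no split brings both centers near 80%.

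**Step 4. What the stated aim would require.** Each center would need 275 evaluable per arm. With the plan's own ×1.2 this is 330 per arm per center: 660 per arm and 1,320 in total. With division by 0.8 it is 344 per arm per center: 688 per arm and 1,376 in total. Neither total appears in the document.

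**The case against.** **The trial is not decided by center.** The primary analysis is one pooled model adjusted for hospital unit, and center is otherwise a subgroup. The Discussion speaks only of insight into contextual differences and a post-hoc look at differences between units. This stands, and it limits the consequence. A reader might infer that the trial heads for a split verdict, since with an equal split and 49% power in each center exactly one would be significant about half the time (2 × 0.492 × 0.508 = 0.50). The documents do not support that reading: no rule makes the trial's conclusion depend on two center tests.

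**The 49% is not a figure in the plan.** It assumes an equal split and the full 20% lost. The Statistical Analysis section specifies intention-to-treat with multiple imputation for the primary outcome, and Table 1 takes events from health records and death certificates, so the loss of information may be smaller. This also stands: the result should be given as a range with its assumption, not as a fact about the trial.

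**Perhaps 330 per arm was meant for each center.** That would roughly meet the aim (78.5% per center with 264 evaluable per arm). The text does not say so. It presents the calculation as being for the multicenter trial and states the sample per arm without reference to center. If it was the intention, the planned total is unclear by a factor of two (660 or 1,320) and the section still needs correcting.

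**Gender subgroups.** A reader might infer that these too are halved samples. No gender split is given, so nothing can be said about their size.

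**The subgroup method may be in the analysis plan.** The sentence on subgroups neither promises separate significance tests nor excludes interaction terms, so it is not itself an error.

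**Conclusion.** The Sample Size Calculation section is wrong as written. It claims a property for each center that its own inputs do not deliver, because 330 per arm is 275 × 1.2 for one comparison.

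Per-center power is about 49% to 58% under an equal split, and lower in the smaller center otherwise (about 41% at 60/40 and 32% at 70/30, after 20% loss). These values rest on 13% against 6% holding in both centers, on an unadjusted two-proportion test, and on the assumed split. The conclusion that both centers cannot be near 80% holds for every split if 330 per arm covers the whole trial, which is the plain reading.

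The pooled primary comparison, its sample size and its analysis are untouched. This is a false statement about the design that should be corrected, not a threat to the main result.

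**What to change.** In the Sample Size Calculation section:

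- Delete the words *at each center*.
- State that 330 per arm, 660 in total, is sized for the pooled comparison adjusted for gender and hospital unit.
- State that center-specific comparisons are not powered. If a figure is given, give a range with its assumption, for example about 49% to 58% under an equal split and less in the smaller center if the split is unequal.
- If 330 per arm in each center was intended, say so and state the total of 1,320.

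As a secondary improvement, judge center effects by a treatment-by-center interaction, showing center estimates with 95% confidence intervals, and not by whether each center is significant on its own.

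Cost: a change of wording, with no additional patients unless the per-center reading was the one intended. The downside is that the stated claim becomes less favorable.

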### Procedures

Sample recruitment will have the support of the clinical staff of the outpatient clinics based on inclusion and exclusion criteria. All eligible participants will be asked to fill out the informed consent. Participants will be randomized at a 1:1 ratio to receive usual care composed by CR alone (control group) or the mHeart.4U program (intervention group). Treatment allocation will follow a computer-generated schedule prepared by a biostatistician. The randomization schedule will be stratified by gender and trial center and will use random permuted blocks (Figure 1). The control group will follow the standard treatment protocol (27), while the Intervention group will, additionally, participate in the mHEART.4U intervention (Figure 1).

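### 330 per arm falls slightly short of the stated 80% power after 20% loss: 264 would remain where about 275 are needed (minor arithmetic error)

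*Protocol article*

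**What the plan says.** Everything needed is printed in the protocol article. Under Sample Size Calculation, the event proportions are taken from a cited systematic review: "a proportion of 6% in the intervention group was rehospitalized compared with 13% in the control group 1 year after the intervention terminus". The test is planned "with a 95% confidence level, two-tailed analysis", with "power (1 -β) of 80%, a significance of 0.05". The section ends: "accounting for 20% loss to follow-up, a sample of 330 patients per arm will be included". Under Procedures, allocation is equal: "Participants will be randomized at a 1:1 ratio". Under Statistical Analysis, the significance level is confirmed: "All statistical tests will be 2-sided at α = 0.05".

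The section names G Power as the software. It does not give the test or formula chosen, the number required before allowing for loss, or how the 20% was applied.

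**The concern.** To have n evaluable patients after losing a fraction d, one must randomise n/(1 - d). Multiplying by (1 + d) gives too few, because the loss is taken from the larger, randomised number. The figure of 330 has the form of the second calculation.

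If so, the sentence that justifies the trial's size is not true on its own terms: 330 per arm, 20% loss and 80% power cannot all hold together for 13% v 6%. At stake is the accuracy of a stated design property that any reader can recompute. The trial's ability to answer its question is hardly touched, because the gap is small.

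**Working it through.** **Inputs.** Control 13%, intervention 6%, difference 7 percentage points, two-sided alpha 0.05 (z = 1.96), power 80% (z = 0.8416), loss 20%, all from Sample Size Calculation; 1:1 allocation from Procedures. The mean proportion is (0.13 + 0.06)/2 = 0.095.

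**Step 1: evaluable patients needed.** Pooled two-proportion formula, no continuity correction:

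n = [1.96 x sqrt(2 x 0.095 x 0.905) + 0.8416 x sqrt(0.13 x 0.87 + 0.06 x 0.94)]² / 0.07²

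= [1.96 x 0.4147 + 0.8416 x 0.4117]² / 0.0049 = 274.2, so **275 per arm** (power 80.1%).

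**Step 2: reproduce the plan's figure.**

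- 275 x 1.20 = **330**, the stated size exactly.
- 275 / (1 - 0.20) = 343.75, so **344**.

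**Step 3: what 330 delivers.**

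- With 20% loss: 330 x 0.80 = 264 evaluable, 11 per arm fewer than 275.
- Loss that 330 can absorb: (330 - 275)/330 = 16.7%.
- Power at 264: z = (0.07 x sqrt(264) - 1.96 x 0.4147)/0.4117 = 0.788, which gives **78.5%**.

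**Step 4: does another formula rescue 330?** The article does not name its formula, so other choices were tried.

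| Formula (two-sided unless noted) | n per arm | n / 0.8 | n x 1.2 |
|---|---|---|---|
| Pooled | 275 | 344 | 330 |
| Unpooled | 272 | 340 | 327 |
| Arcsine | 267 | 334 | 321 |
| Pooled under both hypotheses | 276 | 345 | 332 |
| Continuity-corrected | 303 | 379 | 364 |
| One-sided pooled (not the plan's test) | 216 | 270 | 260 |

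Only the pooled formula with multiplication gives 330. No two-sided formula tried gives 330 or fewer by division; the nearest is arcsine at 334.

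**Step 5: power at 264 per arm by method.** Pooled 78.5%, unpooled 78.9%, exact enumeration of the uncorrected chi-square test 79.4%, arcsine 79.7%. Fisher's exact test gives 75.3% and the continuity-corrected formula 73.9%. The continuity-corrected requirement (303) does not lead to 330 by either route in the table, so it is unlikely to be the basis of the plan's figure. Every two-sided method tried is below 80%.

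**The case against.** **The mechanism is not printed.** This stands. Neither 275 nor the multiplication appears in the article, so one can say only that the loss appears to have been added this way. The exact match makes it much the likeliest reading. The shortfall at 264 per arm does not depend on how 330 was reached.

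**The shortfall is trivial.** Largely right. It is 1.5 percentage points by the pooled formula (80 - 78.5) and 0.3 by arcsine (80 - 79.7). A reader might infer from a mis-stated sample size that the trial is materially underpowered; the figures do not support that.

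**Lost patients may still have a primary outcome.** Table 1 takes the primary events from patient health records and death certificates, so someone who stops attending may still be counted. This stands as a condition: the shortfall arises only if 20% of primary outcomes are missing. With complete outcome data, 330 per arm would have 86.7% power. But the 20% is the plan's own allowance within the primary-outcome calculation, and the Discussion expects higher drop-out in mHealth studies.

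**Multiple imputation keeps everyone in the analysis.** The Statistical Analysis section plans intention-to-treat with imputation. Imputation does not by itself restore the information lost with a missing outcome, so it does not turn 264 observed outcomes into 330.

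**A stronger reading that is not supported.** The section also quotes the review's pooled result: "eHealth CR was effective reducing rehospitalization [RR = 0.49, 95% CI (0.27, 0.89". Since 0.49 x 13% = 6.4% while 6/13 = 0.46, a reader might infer a second slip in the favourable direction. The document does not show one. The 6% and 13% are whole percentages attributed to the review, not described as one multiplied by the risk ratio. Rounded in this way they are compatible with ratios from 0.055/0.135 = 0.41 to 0.065/0.125 = 0.52, which includes 0.49. A pooled risk ratio also need not equal the ratio of crude proportions.

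**Conclusion.** Wrong as written, and minor. On the plan's own inputs, 330 per arm does not give 80% power after a 20% loss. It gives about 78.5% by the formula that reproduces the plan's figure, and up to 79.7% by the most favourable method tried. Against the 344 that match both assumptions, 330 is 14 per arm short: 28 in total, 660 against 688, or about 4%.

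This rests on three assumptions: 13% and 6% are taken as given, the comparison is of two proportions without covariate adjustment, and the 20% loss means 20% of primary outcomes missing in each arm. That the 20% was applied by multiplication is a strong inference from the exact match, not a statement in the article.

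**What to change.** Replace the closing sentence of Sample Size Calculation with wording such as: *275 evaluable patients per arm give 80% power for 13% v 6% at two-sided 0.05; 330 per arm allow for 16.7% loss to follow-up; with 20% loss (264 per arm) power is about 78.5%.* Name the test or formula used in G Power in the same place. If the software output shows a requirement other than 275, the three figures should be recalculated from it.

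This costs one sentence and no patients; the stated power becomes slightly less favourable. If the sponsor prefers to keep both 80% power and 20% loss as stated, the matching size is 344 per arm, at a cost of 28 more patients in total.

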### Statistical Analysis

The patient characteristics in the two arms at baseline will be compared descriptively using chi-squared tests for the binary and categorical variables and an unpaired Student's *t*-test for the continuous variables. One-sample *t*-test will be performed to measure the differences within the same group.

The primary outcome will be analyzed using a generalized linear mixed model, adjusting for the stratification variables (i.e., gender, hospital unit). Logistic regression will be conducted in order to explore predictive relationships of the baseline categorical variables (e.g., age, clinical variables) on the primary outcomes in both groups.

Analyses to determine the study primary outcome will be performed on the principle of intention-to-treat. Accordingly, assuming there will be a reasonable amount (>5%) of missing data, analyses to determine the primary outcome will be conducted using a multiple imputation model. A per-protocol analysis will be conducted with complete cases to test the robustness of intervention effects under different assumptions. Subgroup analyses will be conducted to determine intervention effects by gender and trial center. All statistical tests will be 2-sided at α = 0.05. The biostatistician will remain blinded throughout the analysis of treatment effects.

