Scoping the literature on remote monitoring of cardiovascular patients through mHealth tools, a few clinical study protocols can be found in recent years, aiming at determining the effect of these resources on both clinical (e.g., cardiovascular events) and process outcomes (e.g., hospital readmissions) (22, 23). Although overlapping the effect aimed through the mHeart.4U, the current study protocol adds to the previous as it builds on existing mHeath tools for monitoring and rehabilitation of cardiovascular patients with the integration of AI for personalized selection of the rehabilitation plan. Accordingly, the mHeart.4U trial will aim to reinforce the evidence on outcomes that inform clinical decision-making, such as rehospitalizations and health-related QoL, while following a sustainable approach to intervention research, wherein existing evidence and resources are pragmatically adapted and adopted to fit the real-world practice (24).

The current study protocol will innovatively explore CDSS for management of CVD patients building on existing mHealth-based interventions for cardiac monitoring and rehabilitation. We hypothesize that an mHealth intervention supported by a CDSS will reduce recurrent cardiovascular events, will promote QoL, treatment adherence, adoption of a healthier lifestyle, and Body Mass Index (BMI) reduction. Therefore, the objective of the mHeart.4U clinical study will be to determine the effectiveness of an intervention using a CDSS for remote patient monitoring, selecting the best mHealth tools (apps and wearables) according to the needs of each CVD patient and managing clinical data.

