### Outcomes and Measurements

Outcome measurements will be carried out at the 3-month (T1) and the 6-month interventions (T2) (Table 1).

**Table 1 T1:** Schedule of assessments.

**Assessments**	**Measure**	**T0**	**T1**	**T2**
Recurrent cardiovascular event				
Cardiovascular	Patient health records		x	x
Rehospitalization	Death certificates			
Cardiovascular urgent visit				
Unplanned revascularization				
Cardiovascular mortality				
Worsening heart failure				
Quality of Life	MacNew heart disease health-related Quality of life questionnaire	x	x	x
Adherence to treatment	Therapeutic self-care scale	x	x	x
Anthropometric measures	Patient health records (BMI, waist circumference)	x	x	x
Nutrition	Health-promoting lifestyle profile-II	x	x	x
Physical activity	Health-promoting lifestyle profile-II	x	x	x
Clinical data	Patient health records	x	x	x
Blood pressure, heart rate,	Systematic coronary risk evaluation			
blood biomarkers, pathological				
history, cardiovascular risk				
Sociodemographic Data	Sociodemographic questionnaire	x		
Gender, age, academic				
qualifications, profession				
mHEART.4U usage	Utilization rate, consulted resources, self-monitoring data		x	x

*T0, Baseline assessment; T1, 3-month intervention assessment; T2, 6-month intervention assessment*.

The primary outcome will be the reduction of recurrent cardiovascular events, which is a composite of (i) cardiovascular rehospitalization or urgent visit; or (ii) unplanned revascularization; (iii) cardiovascular mortality; or (iv) worsening heart failure (29, 30).

Secondary outcomes measures will include:

a) Quality of Life, assessed through the MacNew Heart Disease Health-related Quality of Life (HRQL) questionnaire (MacNew) (31).

Acknowledging the importance of including patient's perspectives on health outcomes, the MacNew is a self-reported questionnaire that has been validated and used with both patients with experience of a myocardial infarction, and patients with experience of angina. The measurement instrument is composed of 27 items, scored from 1 (poor) to 7 (high), to assess global HRQL, physical limitations, emotional and social functions. The MacNew is currently validated to many languages including Portuguese, where it appears to be a reliable, valid and moderately responsive instrument to evaluate HRQL of people after a diagnosis of acute coronary syndrome (32);

b) Adherence to treatment, assessed through the Therapeutic Self-care Scale (TSC) (33).

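### The only stated test that fits the repeatedly measured secondary outcomes is a within-arm t-test, which cannot support the between-arm secondary hypotheses

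*Protocol article*

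**What the plan says.** The Statistical Analysis section of the protocol article gives most of its tests a purpose.

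- **Baseline:** "The patient characteristics in the two arms at baseline will be compared descriptively using chi-squared tests", with unpaired t-tests for continuous variables.
- **Change:** the next sentence adds a one-sample t-test, which "will be performed to measure the differences within the same group". It names no outcome and no visit.
- **Primary outcome:** "The primary outcome will be analyzed using a generalized linear mixed model, adjusting for the stratification variables". A logistic regression explores baseline predictors of the same outcome.
- **Analysis set and missing data:** "Analyses to determine the study primary outcome will be performed on the principle of intention-to-treat", and multiple imputation is likewise tied to the primary outcome.
- **Subgroups:** "Subgroup analyses will be conducted to determine intervention effects by gender and trial center", with no outcome or test named.

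All tests are two-sided at 0.05. Table 1 (Outcomes and Measurements) schedules quality of life, adherence, nutrition, physical activity and anthropometric measures at T0, T1 and T2. The Introduction hypothesises that the intervention "will promote QoL, treatment adherence, adoption of a healthier lifestyle, and Body Mass Index (BMI) reduction".

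**The concern.** The secondary hypotheses are about what mHeart.4U adds to usual care. A mean change within one arm cannot isolate that. Under Procedures, the control arm receives cardiac rehabilitation and the intervention arm receives the standard treatment plus mHeart.4U. Under Participants, patients may enter after an acute cardiac event. The Introduction itself credits rehabilitation with better quality of life and physical activity. Improvement in both arms with no mHeart.4U effect is therefore plausible on the document's own account.

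Two misreadings could follow if within-arm p-values carried the inference. A significant improvement in the intervention arm could be credited to mHeart.4U when the controls improved equally. A significant result in one arm and a non-significant one in the other could be taken as a difference between arms, although that difference was never tested. At stake are the claims on quality of life, adherence, lifestyle and BMI. The primary outcome is not affected.

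**Working it through.** **Step 1. Which stated test fits which outcome.** A one-sample t-test of change needs a continuous measure with a baseline value. The primary composite consists of events and has no T0 entry in Table 1, so the test does not fit it. The measures with T0, T1 and T2 entries are the secondary outcomes plus the clinical data (blood pressure, heart rate, biomarkers, cardiovascular risk). The unpaired t and chi-squared tests are assigned to baseline and the mixed model to the primary outcome. That leaves the within-arm test as the only stated one that fits the secondary measures.

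**Step 2. The plan's own figure.** The Sample Size Calculation section gives 13% v 6%, 80% power, two-sided 0.05, 20% loss and 330 per arm. With the pooled-variance formula and mean proportion 0.095:

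n = [1.96 × √(2 × 0.095 × 0.905) + 0.8416 × √(0.13 × 0.87 + 0.06 × 0.94)]² / 0.07² = 274.3, rounded up to 275; 275 × 1.2 = 330.

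The figure reproduces and does not bear on this point. It is used here only for the number of completers: 330 × 0.8 = 264 per arm.

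**Step 3. Behaviour of within-arm tests when there is no intervention effect.** The documents give no SD and no expected change, so the shared mean change d, in SDs of the change score, is an assumption and is shown over a range. In the normal approximation, an arm shows significant improvement with probability p = Φ(d√264 − 1.96), where √264 = 16.25. The arms are independent, so the intervention arm improves significantly and the control arm does not with probability p(1 − p).

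| Shared change d | d√264 | p (each arm) | Intervention only: p(1 − p) |
|---|---|---|---|
| 0 | 0 | 0.025 | 0.024 |
| 0.05 | 0.81 | 0.126 | 0.11 |
| 0.10 | 1.62 | 0.369 | 0.23 |
| 0.15 | 2.44 | 0.683 | 0.22 |
| 0.20 | 3.25 | 0.901 | 0.09 |
| 0.30 | 4.87 | 0.998 | 0.002 |

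A between-arm test holds the two-sided error at 0.05, or 0.025 in favour of the intervention, whatever the shared change. The intervention-only pattern cannot exceed 0.25, since p(1 − p) peaks at p = 0.5 (d about 0.12). For larger shared changes it fades, but the intervention arm's own test is then almost always significant, which misleads in the other way.

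**Step 4. What a between-arm comparison could detect.** With 264 per arm, 80% power and two-sided 0.05, the detectable difference is (1.96 + 0.8416) × √(2/264) = 0.24 SD, before any gain from baseline adjustment.

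**The case against.** The strongest reply is that the link to the secondary outcomes is inferred. The one-sample t-test sentence names no outcome and does not say that any hypothesis will be decided by it. It stands in the paragraph on baseline characteristics, and a within-arm test can sit beside a between-arm one. This is a journal article, and models for secondary outcomes are commonly left to the full protocol or analysis plan, which are not shown. The article's general language also points to comparison: the Methods and Analysis opening describes outcomes of the experimental intervention set against a standard intervention, and the Statistical Analysis section speaks of treatment effects.

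Much of this stands. A reader might infer that the trial will judge its secondary hypotheses without comparing the arms, or that it has no between-arm outcome analysis. The documents support neither. The first is not stated, and the second is contradicted by the mixed model for the primary outcome. The absence of a secondary-outcome model in the article is not in itself a fault.

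What remains is a test that is stated. The section applies the word descriptive to the baseline comparison, not to the within-arm test, and puts all tests at two-sided 0.05. As written it is an inferential procedure, with no natural use except on the secondary and clinical measures, and it cannot answer the hypotheses in the Introduction.

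The baseline p-values are a minor matter of practice. They are called descriptive and affect no conclusion about the intervention.

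**Conclusion.** The concern holds in a limited form. The section states an inferential within-arm test, and no between-arm one, that fits the secondary measures. Used as the basis for the secondary hypotheses, it would give unsupported conclusions.

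For shared changes of 0.05 to 0.20 SD, the false intervention-only pattern has probability about 0.09 to 0.23, against 0.025 in that direction for a between-arm test. At 0.20 SD the intervention arm improves significantly about 90% of the time with no intervention effect. These figures assume 264 completers per arm, equal true change in both arms and a normal approximation; the size of the shared change is not given in the documents.

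It would go too far to say that every secondary conclusion will be wrong. That would need the within-arm test to be the deciding one, no true effect, and a shared change of suitable size for each outcome. The point should be fixed, but it does not threaten the primary analysis or the sample size.

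**What to change.** In the Statistical Analysis section, replace the one-sample t-test as an inferential test with a between-arm comparison for each secondary outcome, adjusted for the T0 value, gender and center. One suitable form is a linear mixed model on the T1 and T2 values with arm, visit and arm-by-visit terms plus those covariates, reporting the between-arm difference at T2 with its 95% CI. Report within-arm changes descriptively, without p-values. If a fuller plan already contains such a model, align the section with it and say that the within-arm summaries are descriptive.

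The cost is wording only. Table 1 already schedules every secondary measure at T0, T1 and T2, gender and center are the stratification factors, and the sample size does not change.
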